## Abstract

**Background::**

Remimazolam, a benzodiazepine ultra-short-acting sedative, has been used in general anesthesia since August 2020. It is used in awake surgeries that require awakening the patient in the middle of the surgery because of its rapid awakening effect as well as antagonistic interactions. If remimazolam has associated anterograde amnesia similar to benzodiazepines, it will have a positive effect on preventing psychological trauma. However, to our knowledge, the effect of remimazolam on anterograde amnesia has not been previously examined.

**Methods/design::**

The aim of this exploratory, open, propofol-controlled, single-center, randomized clinical trial is to examine the effect of remimazolam on postoperative memory retention and delayed regeneration. Seventy patients undergoing breast surgery will be included in the study. The patients will be randomly assigned to receive propofol or remimazolam as sedatives during surgery. The primary endpoint is the number of posters patients remember 24 hours after surgery (among 4 posters shown after awakening from anesthesia) as an assessment of anterograde amnesia. Secondary endpoints are retrograde amnesia, dose of analgesic given from the time the patient returns to the ward until 24 hours after surgery, immediate postoperative pain numerical rating scale scores, and pain numerical rating scale scores 24 hours after leaving the operating room. Recruitment will take place between October 2021 and March 2022 to achieve the target sample size.

**Discussion::**

To our knowledge, this is the first trial designed to examine the effects of remimazolam on postoperative memory retention and delayed regeneration in patients undergoing breast surgery.

**Trial registration::**

This clinical trial was registered at the University Hospital Medical Information Network (UMIN) Center on September 28, 2021 (UMIN-CTR: UMIN000045593).

## Introduction

1

Remimazolam, a benzodiazepine ultra-short-acting sedative, has been used in general anesthesia in Japan since August 2020; it was first implemented in Japan. This medication has similar characteristics as propofol (eg, it is short acting) and is expected to be used in a similar manner. Clinical trials conducted in Japan have reported that its effect on hemodynamics is less than that of propofol and is considered an easy-to-use sedative in patients with unstable circulation.^[1,2]^

Although anesthetics were originally designed to prevent intraoperative awakening, some surgeries (such as brain surgery under awake conditions) require awakening for medical reasons in the middle of the surgery.^[3]^ Traditionally, propofol has been used in such surgeries because it allows for rapid awakening. However, intraoperative awakening inevitably causes patients discomfort during surgery. If that memory persists postoperatively, it may have a traumatic effect on the patient.

Remimazolam has been used in surgeries that require awakening the patient in the mid-surgery because it allows for rapid awakening (similar to propofol and antagonists). Since remimazolam is a benzodiazepine, it is expected to cause anterograde amnesia (similar to other benzodiazepines)^[4,5]^ and to decrease the discomfort caused by intraoperative awakening; this property is expected to have a positive effect on preventing psychological trauma.

Clinically, we observed that patients have no memory of the immediate postoperative period after general anesthesia with remimazolam. In addition, based on postoperative interviews of patients sedated with remimazolam, we found that all patients had no memory of postoperative pupillometry examination, bed transfer, or conversations occurring during and shortly following sedation. However, we cannot conclude that remimazolam causes anterograde amnesia based on the current evidence because there is no established method to evaluate anterograde amnesia, and our observations are anecdotal and obtained within the scope of our practice. Specifically, this study aims to compare the effects of different sedatives used in general anesthesia on memory retention in postoperative patients and to establish a method to evaluate effects on anterograde amnesia in validation clinical trials.

## Methods

2

### Objectives

2.1

The aim of this study is to verify the effects of remimazolam use in general anesthesia on memory retention in postoperative patients and to establish a method to evaluate its effects on anterograde amnesia in validation clinical trials.

### Study design

2.2

The standard protocol items for randomized trials guidelines were followed. The present study is an exploratory, open, propofol-controlled, single-center, randomized controlled trial (RCT) to compare the efficacy and safety of remimazolam with propofol. The study will be conducted by the Department of Anesthesiology and Critical Care Medicine, Kyushu University Hospital. In total, 70 patients aged 20 to 65 years will be randomly assigned to receive remimazolam or propofol as sedative anesthetic agent. The participants will be randomly divided into 2 groups using stratified block randomization. The study design is summarized in Figure 1 and available at URL (https://upload.umin.ac.jp/cgi-open-bin/ctr_e/ctr_view.cgi?recptno=R000052026)).

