### Randomization

2.8

An allocation supervisor appointed by the Data Center of the ARO Clinical Research Promotion Department of Clinical and Translational Center has prepared an allocation table for the purpose of randomization. The electronic data capture software used in this study refers to this allocation table for randomly allocating patients. The allocation ratio was set at 1:1. The detailed procedure of random allocation has not been provided to the researchers. The permuted block randomization block method will be used for allocation.

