#### Analysis of primary and secondary endpoints

2.12.1

Because the goal of this small exploratory study is to generate appropriately powered large-scale RCTs for future, we will perform descriptive statistics using PPS. After evaluation with descriptive statistics, for additional information, analysis of covariance including the baseline value as a covariate will be performed for comparison of groups. If the distribution is greatly skewed in a blinded review, transformation of values such as logarithmic transformation will be considered. As a sensitivity analysis of the primary endpoint, the same analyses will be performed for the PPS. All analyses will be performed with a two-sided significance level of .1.

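### Allocation is described as stratified, but the planned comparison model names no stratification factor; if the strata predict recall, its standard error is overstated

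*Protocol article*

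**What the plan says.** Three sections of the protocol article bear on this.

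- **2.2 Study design:** "The participants will be randomly divided into 2 groups using stratified block randomization". No factor is named. The trial has one centre, so site cannot be the stratum.
- **2.8 Randomization:** "The permuted block randomization block method will be used for allocation". It also says "The allocation ratio was set at 1:1" and "The detailed procedure of random allocation has not been provided to the researchers". Stratification is not mentioned.
- **2.12.1 Analysis of primary and secondary endpoints:** the trial reports descriptive statistics first ("we will perform descriptive statistics using PPS"). As a supplement, "analysis of covariance including the baseline value as a covariate will be performed for comparison of groups". The level is fixed for everything: "All analyses will be performed with a two-sided significance level of .1".

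The baseline value is the only covariate named. The primary endpoint in 2.7.1 is a count, out of four, of posters shown after awakening, so a baseline value for it is not evident.

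**The concern.** Stratified blocks balance the arms on the stratification factors. If a factor predicts the outcome, that balance removes between-stratum variation from the treatment difference. A model without the factor still counts this variation as residual error, so it reports a larger standard error than the estimate really has. The interval is then too wide, and the test rejects less often than its nominal level.

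This matters here because the trial exists to inform a larger one. Section 2.10 justifies 70 patients by the information they will give for the confirmatory trial, so the estimate and its variance are the main product. A residual variance that still contains the stratum component would oversize a confirmatory trial that is analysed with its strata.

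The baseline covariate may not help for the primary endpoint. If no baseline value exists for the poster count, that comparison could reduce to an unadjusted one.

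**Working it through.** **Inputs from the article.** 70 patients, 35 per arm (2.10); 1:1 allocation (2.8); two-sided level 0.10 (2.12.1), so the critical value is z = 1.645. The article gives no standard deviation, effect size or power, so there is no figure of its own to reproduce.

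**Assumptions.** R² is the share of outcome variance that the strata explain and that no other model term already carries. The article gives no value for it, so a range is used. The simulation also assumes one two-level stratum, blocks of 4 and a normal outcome.

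**Formulas.** Let σ² be the total outcome variance.

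- Standard error reported without the strata: σ√(2/35) = 0.239σ.
- Actual standard error when the strata are balanced by design: σ√(1−R²) × √(2/35).
- Ratio of reported to actual: 1/√(1−R²).
- Actual type I error: 2[1 − Φ(1.645/√(1−R²))].

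| Assumed R² | Ratio of standard errors | Actual type I error (nominal 0.10) |
|---|---|---|
| 0 | 1.000 | 0.1000 |
| 0.05 | 1.026 | 0.0915 |
| 0.10 | 1.054 | 0.0829 |
| 0.20 | 1.118 | 0.0659 |
| 0.30 | 1.195 | 0.0493 |

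As an example, take R² = 0.20. The half-width of the 90% interval is reported as 1.645 × 0.239σ = 0.393σ. With the strata in the model it would be about 0.393σ × √0.80 = 0.352σ. The residual variance carried forward is too large by a factor of 1/0.80 = 1.25.

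**Simulation check** (70 patients, 10,000 null trials per setting):

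| Allocation | Model | R² | Ratio of standard errors | Type I error |
|---|---|---|---|---|
| Stratified | without strata | 0 | 1.000 | 0.096 |
| Stratified | without strata | 0.10 | 1.046 | 0.082 |
| Stratified | without strata | 0.30 | 1.179 | 0.051 |
| Stratified | with strata | 0 to 0.30 | 0.989 to 1.000 | 0.096 to 0.102 |
| Not stratified | without strata | 0 to 0.30 | 0.990 to 0.996 | 0.100 to 0.103 |

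The Monte Carlo error at 0.10 is √(0.1 × 0.9/10,000) = 0.003. The simulation agrees with the formula; the small shortfall in the ratio at R² = 0.30 is what incomplete final blocks would produce. Adding the strata restores the level. When allocation is not stratified, omitting the factor does not distort the standard error.

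**The case against.** Four arguments run the other way.

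1. **The two randomisation statements do not contradict each other.** Stratified block randomisation is usually permuted blocks run within strata. A reader might infer from 2.2 and 2.8 that one of them must be wrong; the text does not support that. The allocation details were deliberately withheld from the researchers and the article is condensed, so the missing list of factors is not a fault in itself. This stands.
2. **The model sentence may not be exhaustive.** It says the baseline value is included, not that nothing else is, and a full covariate list may sit in an analysis plan that is not shown. A reader might infer that the strata will be ignored; the article does not say so. This stands as a limit. Even so, the article names a stratified design and a covariate, and the two do not correspond.
3. **The size is assumed.** No stratum, block size or R² is given, and the population is narrow: one centre, women, aged 20 to under 65, one type of surgery, impaired cognition excluded. R² could be small or zero. The calculation also has no baseline covariate, and one that carried the same information would shrink the effect. This stands, and is why the range starts at zero.
4. **The consequence is modest.** The trial is exploratory, the covariance analysis supplements descriptive statistics, and any error costs precision without adding false positives. This lowers the priority but does not remove the mismatch.

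**Conclusion.** The mismatch holds: the article states a stratified design and a comparison model that names no stratification factor. Followed as written, the plan would analyse a stratified trial without its strata.

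The numerical consequence is conditional. It needs allocation to be stratified in fact, the factor to predict recall, and no other term in the model to carry that information. Under those conditions and an assumed R² of up to 0.30, the standard error is overstated by up to about 20% and the type I error falls to about 0.05 against a nominal 0.10. If any condition fails, the effect is nil or smaller.

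A reader might conclude that the standard error will be too large. The article does not support that: it does not show that the strata are prognostic, and 2.8 does not confirm that they exist. The textual mismatch is certain; its size is unknown. The direction is conservative throughout.

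**What to change.** - In 2.8, state whether allocation is stratified. If it is, name the factors as far as concealment allows. The block size can stay withheld.
- If it is stratified, add the stratification factors as covariates to the analysis of covariance in 2.12.1, for the primary and secondary endpoints.
- If it is not, delete the word stratified from 2.2.

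The cost is a sentence in 2.8 and a clause in 2.12.1, or one deleted word. No patients or assessments are added, because a factor used to stratify must already be known when a patient is allocated. One two-level factor takes one residual degree of freedom (68 to 67 with 70 patients and no other covariate). The change should be made before outcomes are compared by arm.

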**Figure 1 F1:**
[figure not shown]
Study design.

### Investigational drug

2.3

Remimazolam is a standard sedative commonly used in clinical practice. It is similar to the benzodiazepine-like drug midazolam, which is also widely used in clinical settings. Remimazolam differs from midazolam in that its metabolites have no pharmacological effects and its sedative effects disappear rapidly upon the discontinuation of administration. The study drug (remimazolam: mundipharma K.K., Tokyo, Japan) is initiated at 6 mg/kg/h, which is changed to 1 mg/kg/h after confirming sleep. During surgery, the dose should be adjusted as required in the range of 0.5 to 2 mg/kg/h with reference to the bispectral index (BIS) value.

The initial dose of control dug (propofol: Maruishi Pharmaceutical Co., Ltd, Osaka, Japan) is 3 μg/mL and is administered using a target-controlled infusion pump and is adjusted with reference to the BIS value.

While the patient is still unconscious, flumazenil should be administered 5 minutes after the surgery ends. Flumazenil is intravenously and slowly administered at an initial dose of 0.2 mg. If the patient's wakefulness level is not sufficiently achieved within 4 minutes after administration, an additional 0.1 mg should be administered. If necessary, 0.1 mg should be administered at 1-minute intervals, up to a total dose of 1 mg.

For concomitant medications, the usual dosage of fentanyl and remifentanil for intraoperative analgesia should be administered. The dosage of remifentanil should not exceed a maximum of 0.5 μg/kg/min. A contraindication that should be considered is that antihistamines should not be administered between the day prior to surgery and the day after surgery.

### Inclusion criteria

2.4

The following criteria are necessary to meet eligibility requirements for the current study.

(1)Patients must provide written informed consent of their own free will.(2)Patients must be aged ≥20 years and must be <65 years.(3)Patients must be undergoing breast surgery under general anesthesia.

In breast surgery cases, intraoperative techniques are relatively uniform, and there are slight individual differences in the degree of invasion. This is because the dosage of analgesics and sedatives does not vary greatly. Although the study will be conducted only in women, there were no reports of differences in memory retention between men and women. Therefore, priority was given to unification of the degree of invasion.

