#### Secondary endpoints

2.7.2

(1)Retrograde amnesia, based on the number of events remembered from prior to the start of anesthesia – ambulatory entry, bed transfer, vein insertion, BIS monitor attachment to the forehead, and mask fitting – and whether the patient remembers the poster (see Figure S2, Supplemental Digital Content, which illustrates the numeric characters) shown before the induction of anesthesia.(2)The dose of analgesic medication administered from the time the patient returns to the ward until 24 hours after surgery.(3)Immediate postoperative pain numerical rating scale (NRS) values (see Figure S3, Supplemental Digital Content, which illustrates the NRS).(4)Pain NRS scores 24 hours after leaving the operating room.

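### Planned operation is not named as a covariate for the pain and analgesic comparisons, although any breast operation is eligible: a possible, minor loss of precision

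*Protocol article*

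**What the plan says.** All references are to the protocol article.

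- **Eligibility (2.4).** The only surgical criterion is "Patients must be undergoing breast surgery under general anesthesia". Neither 2.4 nor the exclusion criteria in 2.5 limit the type or extent of operation.
- **Homogeneity (2.4).** The article states: "In breast surgery cases, intraoperative techniques are relatively uniform, and there are slight individual differences in the degree of invasion". The sentence that follows as explanation is "This is because the dosage of analgesics and sedatives does not vary greatly". No figures are given for either statement.
- **Endpoints (2.7.2).** Three of the four secondary endpoints are postoperative pain or analgesic measures: "The dose of analgesic medication administered from the time the patient returns to the ward until 24 hours after surgery"; "Immediate postoperative pain numerical rating scale (NRS) values"; and "Pain NRS scores 24 hours after leaving the operating room".
- **Analysis (2.12.1).** Descriptive statistics come first. The group comparison is then introduced with "After evaluation with descriptive statistics, for additional information", and the method is "analysis of covariance including the baseline value as a covariate will be performed for comparison of groups". No other covariate is named.
- **Allocation (2.2 and 2.8).** Section 2.2 calls the randomisation stratified but names no factor. Section 2.8 mentions only permuted blocks.

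**The concern.** Breast operations under general anaesthesia can differ in how much tissue is removed and whether the axilla is dissected. These features plausibly predict how much a patient hurts and how much analgesic she receives on the ward. The support offered in 2.4 concerns intraoperative technique and drug dosage. That does not show that pain on the ward is uniform, and analgesic use on the ward is itself an outcome here.

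The analysis does choose an adjustment, but it fits these endpoints poorly. Analgesic dose from the return to the ward has no evident pre-treatment value. The text also describes no preoperative pain score (the schedule in Figure 2 was not available for this check). As written, the analgesic comparison would be effectively unadjusted, and the two pain comparisons may be as well.

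At stake is the width of the intervals for secondary endpoints 2 to 4. These matter mainly as input to the later confirmatory trial that the article has in view.

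**Working it through.** **Inputs from the article.** 35 patients per arm, N = 70 (2.10); 1:1 allocation (2.8); two-sided level 0.10 (2.12.1). There is no power calculation, effect size, variance or operation mix, so there is no plan figure to reproduce beyond 2 × 35 = 70.

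**Assumption.** R² is the share of an endpoint's variance explained by planned operation. The documents do not give it. The range 0 to 0.20 is used here; 0 represents the article's own position taken at its strongest.

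**What R² could mean.** For a binary factor with share q of larger operations and a shift of g within-group SDs, R² = q(1−q)g² / [1 + q(1−q)g²]. With q = 0.3 (assumed), q(1−q) = 0.21:

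- g = 0.3: 0.0189 / 1.0189 = 0.02
- g = 0.5: 0.0525 / 1.0525 = 0.05
- g = 0.8: 0.1344 / 1.1344 = 0.12
- g = 1.0: 0.21 / 1.21 = 0.17

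**Effect of adjusting.** With k covariate terms, the ratio of adjusted to unadjusted variance is about (1 − R²) × (N − 3)/(N − 3 − k). The second factor is the price of estimating the extra terms. For N = 70 and k = 1 it is 67/66 = 1.015. The interval width changes by the square root of the ratio, and the equivalent N is 70 divided by the ratio.

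| R² | Variance ratio | Change in CI width | Equivalent N | Power at an assumed 0.5 SD effect |
|---|---|---|---|---|
| unadjusted | 1 | – | 70 | 67.2% |
| 0 | 1.015 | +0.8% | 69 | 66.7% |
| 0.05 | 0.964 | −1.8% | 73 | 68.6% |
| 0.10 | 0.914 | −4.4% | 77 | 70.7% |
| 0.20 | 0.812 | −9.9% | 86 | 75.1% |

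A simulation for k = 1 (20,000 replicates per value, 30% in one category) gave variance ratios of 1.015, 0.965, 0.907 and 0.815 for the same four R² values, in agreement.

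**Break-even.** Adjustment pays once R² exceeds k/67: about 0.015 for one term, 0.030 for two and 0.045 for three. A shift of 0.3 SD in 30% of patients (R² about 0.02) already passes break-even with one term, but not with three.

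**If operation type is a stratum.** Suppose operation type is one of the unnamed factors in 2.2 and the model omits it. The unadjusted test is then conservative. Its true two-sided level is about 2[1 − Φ(1.645/√(1−R²))], which is 0.083 at R² = 0.10 and 0.066 at R² = 0.20, against the nominal 0.10.

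**The case against.** **Operation may not be left out at all.** A reader might infer from 2.12.1 that the plan excludes it. The text does not support that. It says the model includes the baseline value, which does not rule out further covariates. The article is condensed, the analysis plan is not shown, and the strata in 2.2 are unnamed. What stands is narrower: the one covariate that is fixed has no evident counterpart for ward analgesic dose.

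**Chance imbalance is not bias.** A reader might also infer that more large operations in one arm would pass as a drug effect. If 40% of operations were larger and allocation were not stratified on operation, the between-arm difference in that share would have an SD of √(2 × 0.4 × 0.6/35) = 11.7 percentage points, so imbalances do occur. Under randomisation, however, they are random error that the unadjusted interval already covers. They are the same lost precision seen from another side, not a second harm. The 11.7-point figure also fails if operation is a stratum.

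**The gain may be nil.** If extent really varies only slightly, R² is near zero and adjusting loses a little. It is therefore not free: each term costs about 1.5% of variance, and a finely divided factor could cost more than it returns. Analysis in the per-protocol set, which may be smaller than 70, raises that cost somewhat. This objection stands, and it is why a single binary term is preferable.

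**Low stakes.** The trial is exploratory and the covariance analysis supplements descriptive statistics. The endpoints concerned are secondary. This stands and limits the severity.

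**Conclusion.** The point holds as a minor one. The article admits any breast operation, asserts near-uniform extent without data, and names a single covariate that does not evidently exist for ward analgesic dose. The supplementary comparisons of secondary endpoints 2 to 4 may therefore lose precision.

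The documents do not allow the loss to be sized. Under the assumed R² range and N = 70, one binary term moves the interval width from about +0.8% (R² = 0) to about −10% (R² = 0.20). The case for acting rests on this asymmetry: under 1% wider if the uniformity claim is right, about 4% to 10% narrower if operation explains 10% to 20% of the variance. The documents support no conclusion of bias, and nothing here touches the poster-recall primary endpoint.

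**What to change.** In section 2.12.1, state that planned operation, as scheduled before allocation, enters the analysis of covariance for secondary endpoints 2 to 4 as one binary factor (lesser versus greater extent, with the division defined in advance). Use the planned operation rather than the one performed, so that the covariate is fixed before randomisation. Show its distribution by arm.

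Name the stratification factors in 2.2 and 2.8. If operation type is among them, the same term belongs in the model for that reason.

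The cost is a sentence or two, recording the planned operation before allocation, and one degree of freedom: about 1.5% of variance if operation proves not to be prognostic, slightly more if the per-protocol set falls below 70.
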